**General Information and Abstract of the Proposal**

**Title of the Project:**
Investigating the Effect of Using Autologous Amniotic Membrane and Fluid on Wound Healing and Complications of Cesarean Surgery: A Factorial Randomized Clinical Trial.

**Keywords:**
Wound healing and complications of cesarean surgery, autologous amniotic membrane and fluid

**Type of Study:**
Randomized Clinical Trial

**Summary of the Necessity of the Study:**
Human amniotic membrane and fluid have been used for wound healing (acute and chronic) and burn treatment since the early 20th century. As previously confirmed, their use can reduce healing time, infection, and pain. Studies have shown that the amniotic membrane can induce endothelial cell migration and angiogenesis. A recent meta-analysis demonstrated that patients with chronic lower limb wounds treated with amniotic membrane showed significantly higher healing success over six weeks compared to those with standard care dressings. Furthermore, it has been found that human cryopreserved viable amniotic membrane (hCVAM) can inhibit bacterial growth in wounds, likely due to two antimicrobial peptides, HBD2 and HBD3.

**Summary of Method and Analysis Techniques:**
This study is a prospective, interventional, randomized, controlled, factorial, double-blind clinical trial conducted at Arash Women's Hospital among pregnant women scheduled for cesarean section. The intervention groups are:

- Group A: Dressing with autologous amniotic membrane
- Group B: Dressing with autologous amniotic fluid spray
- Group C: Combination of autologous membrane and fluid spray
- Group D: Standard cesarean wound dressing (control)

Amniotic fluid and membrane are obtained from the patient herself and applied at each wound closure stage. Outcomes will be assessed on postoperative days 2, 10, and 28.

**Is this an international collaborative study?**
No

**Introduction – Problem Statement:**
Cesarean section, widely adopted since James Munro Kerr introduced improved techniques in the early 20th century, has saved many lives. With the increasing number of cesarean procedures, it's now frequently described as an epidemic. Globally, cesarean rates rose from 6.7% in 1990 to 19.1% in 2014. In Iran, the rate is as high as 48%, far exceeding the WHO's recommended 15%, highlighting the importance of addressing associated complications.

The increased preference for cesarean in Iran can be categorized into social-demographic, obstetric-clinical, and non-obstetric-non-clinical factors. Higher education and maternal age are major socio-demographic factors, while prior cesareans and fetal distress are clinical contributors. Non-clinical factors include fear of vaginal birth and physician recommendation. Cesareans offer benefits such as perineal protection, reduced urinary incontinence, reduced fear of labor pain, and quicker recovery.

However, cesareans carry risks such as surgical site infections (SSIs), endometritis, and wound complications like seromas and hematomas, affecting 3–15% of cases. Proper wound dressing significantly influences healing. Negative Pressure Wound Therapy (NPWT) reduces SSI risk but is costly and not cost-effective in low-risk patients.

Amniotic membrane has been historically used for wound healing and burns. It promotes endothelial cell attraction and angiogenesis. Meta-analyses show superior healing in chronic wounds compared to standard care. hCVAM also inhibits bacterial growth via peptides HBD2 and HBD3. Frozen amniotic membranes are now available for wound dressings.

Given the advantages of autologous grafts—lower immune response, reduced disease transmission risk, better outcomes, easier access, lower cost, and fewer ethical concerns—this study investigates the effects of using autologous amniotic membrane and fluid on cesarean wound healing and complications.

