**Specific Objectives of the Study:**

1. To assess the effect of amniotic membrane on wound healing using the POSAS scale on days 10 and 28 post-surgery
2. To evaluate the effect of amniotic membrane on surgical site infection
3. To assess the effect of amniotic membrane on wound dehiscence
4. To assess the effect of amniotic membrane on hematoma formation
5. To assess the effect of amniotic membrane on seroma formation
6. To assess the effect of amniotic membrane on pain at 4, 12, 24, and 36 hours after surgery
7. To assess the effect of amniotic membrane on the frequency of injected analgesic use in the first 36 hours
8. To evaluate the effect of amniotic membrane on the incidence of any adverse events
9. To assess the effect of amniotic membrane on the duration of hospitalization
10. To assess the effect of sprayed amniotic fluid on wound healing using the POSAS scale on days 7 and 28 post-surgery
11. To evaluate the effect of sprayed amniotic fluid on surgical site infection
12. To assess the effect of sprayed amniotic fluid on wound dehiscence
13. To assess the effect of sprayed amniotic fluid on hematoma formation
14. To assess the effect of sprayed amniotic fluid on seroma formation
15. To assess the effect of sprayed amniotic fluid on pain at 4, 12, 24, and 36 hours after surgery
16. To assess the effect of sprayed amniotic fluid on the frequency of injected analgesic use in the first 36 hours
17. To evaluate the effect of sprayed amniotic fluid on the incidence of any adverse events
18. To assess the effect of sprayed amniotic fluid on the duration of hospitalization
19. To assess the combined effect of membrane and fluid on wound healing using the POSAS scale on days 10 and 28
20. To evaluate the combined effect on surgical site infection
21. To assess the combined effect on wound dehiscence
22. To assess the combined effect on hematoma formation
23. To assess the combined effect on seroma formation
24. To assess the combined effect on pain at 4, 12, 24, and 36 hours post-surgery
25. To assess the combined effect on the frequency of injected analgesic use in the first 36 hours
26. To evaluate the combined effect on the incidence of adverse events
27. To assess the combined effect on hospital stay duration
28. To compare the effects of membrane vs. fluid on wound healing (POSAS) on days 10 and 28
29. To compare membrane, fluid, and combination regarding surgical site infection
30. To compare the groups regarding wound dehiscence

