31. To compare the groups regarding hematoma formation
32. To compare the groups regarding seroma formation
33. To compare the groups regarding pain at 4, 12, 24, and 36 hours post-surgery
34. To compare the groups regarding injected analgesic use in the first 36 hours
35. To compare the groups regarding adverse events
36. To compare the groups regarding length of hospital stay

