**Exclusion Criteria:**

- Unwillingness to participate
- BMI ≥40 at enrollment
- Placenta previa or placenta accreta
- Previous bowel or urologic surgery
- Multiple gestation
- Known or suspected immunodeficiency (e.g., HIV, Hepatitis B/C)
- Use of immunosuppressive drugs
- Known tobacco or substance use
- Any condition deemed risky by the investigator
- History of keloid formation
- Chorioamnionitis or systemic infections at admission, including subcutaneous infections
- Need for emergency cesarean (e.g., fetal distress, placental abruption, severe preeclampsia/eclampsia)
- Ruptured membranes prior to surgery
- Amniotic fluid stained with meconium or blood
- Multiple vaginal examinations
- Severe preeclampsia with symptoms

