**Statistical Analysis:**
Analysis will be performed using Stata 17.0. Normality will be assessed via statistical tests, graphical evaluation, and skewness/kurtosis. One-way ANOVA and Kruskal-Wallis tests will be used for parametric and non-parametric continuous variables, respectively. Chi-square or Fisher’s Exact tests will be used for proportions. A p-value <0.05 is considered statistically significant. For participants who discontinue or are lost to follow-up, available data will be included. Interim analysis will be performed at 50% enrollment, with p < 0.001 considered significant.

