**Sample Size Calculation:**
Based on the study by Cromi et al. (16), which compared cesarean wound healing and pain across four suturing techniques, the following assumptions were made:

- POSAS patient score mean = 19.3 (SD = 7.5)
- POSAS observer score mean = 20.6 (SD = 7.6)
- VAS mean pain score = 8 (SD = 1.7)
  With a significance level (alpha) of 5% and power of 90% to detect a 25% reduction in wound healing and pain scores, the highest calculated required sample size was 51 per group. Allowing for a 10% attrition rate, the final sample size is set at 56 participants per group, totaling 224 participants across four groups.

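### Complications are in every main objective, but the trial is sized only on scar and pain scores, and the protocol names no factorial comparison for them

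*Protocol*

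**What the plan says.** The four main objectives each pair wound healing with complications. Under Specific Objectives, items 2–5, 11–14, 20–23 and 29–32 take infection, dehiscence, hematoma and seroma separately for membrane, fluid, the combination and the between-group comparison. Typical items are "To evaluate the effect of amniotic membrane on surgical site infection" and "To compare the groups regarding seroma formation". That makes 4 × 4 = 16 objectives.

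The Introduction gives one rate. It follows a list of surgical site infection, endometritis and "wound complications like seromas and hematomas, affecting 3–15% of cases". No rate is given for any one of the four outcomes.

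The Sample Size Calculation rests on scores alone: "With a significance level (alpha) of 5% and power of 90% to detect a 25% reduction in wound healing and pain scores". It reports that "the highest calculated required sample size was 51 per group" and, after attrition, "the final sample size is set at 56 participants per group, totaling 224 participants across four groups".

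On analysis the protocol says "Chi-square or Fisher’s Exact tests will be used for proportions", with p<0.05 as the threshold. The title and design section call the trial factorial, but the Statistical Analysis section names no comparison of women with and without membrane, or with and without fluid. No composite complication outcome is defined.

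**The concern.** The objectives promise answers on complications, and the ethics section bases the interventions partly on a hypothesis of reduced infection. The fixed sample size was never checked against an event rate. If events are few, a p<0.05 rule applied to each complication has little chance of separating a useful intervention from a useless one. Comparing single arms of 56 also gives up the main advantage of a 2 × 2 design, in which every woman contributes to the estimate for both interventions. The stake is what the trial can claim about complications. The scar and pain outcomes are not affected.

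**Working it through.** **1. The protocol's own figure.** n per group = 2(z₀.₉₇₅ + z₀.₉₀)² SD²/δ², with δ = 25% of the mean and (1.960 + 1.282)² = 10.507.

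- POSAS patient: δ = 0.25 × 19.3 = 4.825; n = 2 × 10.507 × 7.5²/4.825² = 50.8, so 51.
- POSAS observer: δ = 0.25 × 20.6 = 5.15; n = 2 × 10.507 × 7.6²/5.15² = 45.8, so 46.
- VAS: δ = 0.25 × 8 = 2; n = 2 × 10.507 × 1.7²/2² = 15.2, so 16.

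The largest is 51, and 51 × 1.1 = 56.1. The stated 51 and 56 reproduce, so the sizing is sound for the scores. No proportion enters it.

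**2. Expected events.** At 3–15% for complications pooled, a control group of 56 expects 56 × 0.03 = 1.7 to 56 × 0.15 = 8.4 events. Split evenly over four outcomes (an assumption), the rate is 0.75–3.75% each, or 0.4–2.1 events.

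**3. Events needed.** Against zero events in the comparison group, two-sided Fisher gives p = 0.057 for 5 of 56 and p = 0.027 for 6 of 56. For 112 against 112, 6 against 0 gives p = 0.029. Six events are therefore needed in both cases.

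**4. Probability of p<0.05.** For a halving, binomial probabilities are summed over all tables with Fisher p<0.05. For complete prevention, the probability is P(X ≥ 6), X ~ Bin(56, r) or Bin(112, r).

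| Rate r without the intervention | Halving, 56 v 56 | Halving, 112 v 112 | Complete prevention, 56 v 56 | Complete prevention, 112 v 112 |
|---|---|---|---|---|
| 3% | 0.3% | 3% | 0.7% | 12% |
| 3.75% | 0.7% | 5% | 2% | 24% |
| 5% | 2% | 8% | 6% | 49% |
| 7% | 4% | 14% | 20% | 80% |
| 10% | 8% | 22% | 49% | 97% |
| 15% | 15% | 34% | 86% | >99% |

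The 112-against-112 columns give the whole side without the intervention the rate r, that is, they assume the other intervention does nothing. If it also works, events are fewer. With 51 evaluable per arm, the largest halving figures fall to 13% (51 v 51) and 32% (102 v 102). For 80% power to detect a halving, the normal approximation gives 278 per arm at 15% and 1,534 at 3%.

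**5. Gain from the margins.** The standard error of a risk difference scales with 1/√n, so moving from 56 to 112 per side multiplies the interval width by √(56/112) = 0.71, about 30% narrower. For 15% against 7.5%, the 95% half-width is 1.96 × √[(0.15 × 0.85 + 0.075 × 0.925)/n]: 11.6 percentage points at n = 56 and 8.2 at n = 112.

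**The case against.** Trials routinely list complications that they are not powered for, and exploratory labels are often left to an analysis plan, which is not shown here. That is fair: low power on outcomes with no power claim is not an error in itself. But the objectives and sample size are protocol content, and here complications stand in every main objective.

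The rate per complication is unknown. The even split treats the four outcomes as mutually exclusive, although one woman may have both infection and dehiscence. The 3–15% may also be read as attaching only to seromas and hematomas. This stands, so a reader who infers that even complete prevention could never show goes too far: at 7–10% the margins would show it with 80–97% probability. The halving result needs no split, because it holds even if one outcome took the full 15%.

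The choice of test matters. The protocol does not ask for sixteen pairwise tests, and four four-group tests could serve the objectives. There, 4 control events with none elsewhere already give exact p = 0.014, but the chance of 4 or more among 56 is 16% at 3.75% (82% at 10%). An uncorrected chi-square would also accept 4 against 0. At 4% that gives 19% for 56 v 56 and 66% for 112 v 112, but with expected counts near 2 per group, where Fisher is the usual choice. For a halving from 15%, the normal approximation still gives only 22% (51 v 51) and 40% (102 v 102).

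A reader might also infer from exclusions such as "Chorioamnionitis or systemic infections at admission, including subcutaneous infections" that high-risk women have all been removed. Many are excluded, but women with BMI below 40 remain eligible and diabetes is not listed. The effect on event rates cannot be computed from the protocol, and the figures above make no allowance for it.

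**Conclusion.** The point holds as a gap between the objectives and the design. For a halving of risk, a single complication has at most about 15% power on a 56-against-56 comparison and 34% on the 112-against-112 margins, anywhere in the protocol's 3–15% range, by two-sided Fisher with no attrition. The further statement, that complete prevention would usually miss p<0.05, depends on component rates of about 4–5% or less, on Fisher's test, and on pairwise or marginal comparisons.

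It would be tempting to add that null results will be read as no effect. The protocol does not say so; it only defines p<0.05 as significant. What can be said is that it states no safeguard against that reading. The POSAS and VAS sizing is unaffected.

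**What to change.** - Define any wound complication (infection, dehiscence, hematoma or seroma) by week 4 as the main complication outcome, from data the follow-up visits already collect for the separate objectives.
- Estimate the effect of membrane (groups A and C against B and D) and of fluid (B and C against A and D) as risk differences with 95% confidence intervals on the 112-against-112 margins. This answers main objectives 1 and 2 directly.
- Report the four components by group as counts.
- State in the objectives that those on complications are estimation only, and that a non-significant result is not evidence of no effect.

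The cost is wording in the objectives and analysis sections, with no new patients, visits or data. The composite mixes complications of different seriousness, so the components must stay visible. It is itself underpowered: 34% for a halving from 15% and 14% from 7% on the margins. Each marginal estimate averages over use of the other intervention. Confirmatory claims on single complications are given up.

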**Literature Review:**

- *Mohseni et al.* (2018): In a randomized clinical trial, autologous amniotic membrane dressing reduced post-cesarean pain and analgesic use compared to standard dressing, as measured by VAS.
- *Molazem et al.* (2018): A double-blind trial showed improved wound healing using amniotic membrane, assessed via the REEDA scale.
- *Serena et al.* (2020): A randomized clinical trial on diabetic foot ulcers found significantly higher wound closure rates at weeks 12 and 16 in patients treated with cryopreserved amniotic membrane compared to standard care.

**General, Specific, and Practical Objectives**

**Main Objectives of the Study:**

1. To investigate the effect of autologous amniotic membrane on cesarean wound healing and complications
2. To investigate the effect of sprayed autologous amniotic fluid on cesarean wound healing and complications
3. To assess the effect of simultaneous use of autologous amniotic membrane and sprayed fluid on cesarean wound healing and complications
4. To compare the effects of amniotic membrane, sprayed amniotic fluid, and their combined use on cesarean wound healing and complications

**Specific Objectives of the Study:**

1. To assess the effect of amniotic membrane on wound healing using the POSAS scale on days 10 and 28 post-surgery
2. To evaluate the effect of amniotic membrane on surgical site infection
3. To assess the effect of amniotic membrane on wound dehiscence
4. To assess the effect of amniotic membrane on hematoma formation
5. To assess the effect of amniotic membrane on seroma formation
6. To assess the effect of amniotic membrane on pain at 4, 12, 24, and 36 hours after surgery
7. To assess the effect of amniotic membrane on the frequency of injected analgesic use in the first 36 hours
8. To evaluate the effect of amniotic membrane on the incidence of any adverse events
9. To assess the effect of amniotic membrane on the duration of hospitalization
10. To assess the effect of sprayed amniotic fluid on wound healing using the POSAS scale on days 7 and 28 post-surgery
11. To evaluate the effect of sprayed amniotic fluid on surgical site infection
12. To assess the effect of sprayed amniotic fluid on wound dehiscence
13. To assess the effect of sprayed amniotic fluid on hematoma formation
14. To assess the effect of sprayed amniotic fluid on seroma formation
15. To assess the effect of sprayed amniotic fluid on pain at 4, 12, 24, and 36 hours after surgery
16. To assess the effect of sprayed amniotic fluid on the frequency of injected analgesic use in the first 36 hours
17. To evaluate the effect of sprayed amniotic fluid on the incidence of any adverse events
18. To assess the effect of sprayed amniotic fluid on the duration of hospitalization
19. To assess the combined effect of membrane and fluid on wound healing using the POSAS scale on days 10 and 28
20. To evaluate the combined effect on surgical site infection
21. To assess the combined effect on wound dehiscence
22. To assess the combined effect on hematoma formation
23. To assess the combined effect on seroma formation
24. To assess the combined effect on pain at 4, 12, 24, and 36 hours post-surgery
25. To assess the combined effect on the frequency of injected analgesic use in the first 36 hours
26. To evaluate the combined effect on the incidence of adverse events
27. To assess the combined effect on hospital stay duration
28. To compare the effects of membrane vs. fluid on wound healing (POSAS) on days 10 and 28
29. To compare membrane, fluid, and combination regarding surgical site infection
30. To compare the groups regarding wound dehiscence
31. To compare the groups regarding hematoma formation
32. To compare the groups regarding seroma formation
33. To compare the groups regarding pain at 4, 12, 24, and 36 hours post-surgery
34. To compare the groups regarding injected analgesic use in the first 36 hours
35. To compare the groups regarding adverse events
36. To compare the groups regarding length of hospital stay

**Study Execution Method**

**Design:**
This is a prospective, interventional, randomized, controlled, factorial, and double-blind clinical trial.

**Study Location:**
Arash Women's Hospital

**Study Population:**
Pregnant women referred to Arash Hospital for cesarean delivery.

**Inclusion Criteria:**

- Age 18–45 years
- Singleton pregnancy
- Scheduled cesarean delivery
- Gestational age ≥36 weeks at the time of delivery
- Hemoglobin >10 g/dL
- Able to provide informed consent
- Willing to be available throughout the study period and complete all related study steps, including follow-up visits and phone calls

**Exclusion Criteria:**

- Unwillingness to participate
- BMI ≥40 at enrollment
- Placenta previa or placenta accreta
- Previous bowel or urologic surgery
- Multiple gestation
- Known or suspected immunodeficiency (e.g., HIV, Hepatitis B/C)
- Use of immunosuppressive drugs
- Known tobacco or substance use
- Any condition deemed risky by the investigator
- History of keloid formation
- Chorioamnionitis or systemic infections at admission, including subcutaneous infections
- Need for emergency cesarean (e.g., fetal distress, placental abruption, severe preeclampsia/eclampsia)
- Ruptured membranes prior to surgery
- Amniotic fluid stained with meconium or blood
- Multiple vaginal examinations
- Severe preeclampsia with symptoms

**Interventions:**

- **Group A:** Dressing with autologous amniotic membrane
- **Group B:** Dressing with sprayed autologous amniotic fluid
- **Group C:** Combination of both membrane and fluid
- **Group D (Control):** Standard dressing

In Group A, a piece of the patient's own amniotic membrane (sized to the surgical incision) is washed with sterile normal saline and placed on the wound before standard dressing. In Group B, extracted amniotic fluid is sprayed (method detailed below). Group C receives both interventions. Group D receives only standard care dressing.

**Intraoperative Variables Recorded:**

- Time of incision
- Time of uterine incision
- Amniotic fluid description (color, presence of vernix, blood, or meconium)
- Time of uterine closure
- End of surgery
- Estimated blood loss
- Type of skin closure

**Amniotic Fluid Spray Protocol:**

1. After uterine incision, the amniotic sac is opened using an amniotic perforator.
2. A 10-mL syringe collects fluid from the amniotic cavity.
3. The fluid is checked for contamination (e.g., meconium), then attached to the spray device.
4. Fluid is sprayed over the closed uterine incision and lower uterine segment.
5. Fascia is closed, then sprayed with 1.5–2.0 mL of fluid.
6. Subcutaneous tissue and skin are each closed and sprayed with 1.5–2.0 mL.
7. The wound is dressed as usual.

**Follow-Up Schedule:**

1. **Discharge Visit (Day 2–3 post-op):**
   - Evaluation of incision (redness, swelling, firmness, pain at rest and with pressure)
   - Analgesic use since delivery
   - Schedule first follow-up (8–12 days post-op)
   - Review vital signs and document fever (>38°C) and actions taken
   - Record any adverse events
2. **Day 7 Visit (Day 8–12 post-op):**
   - Wound assessment
   - Document signs/symptoms of infection
   - Record adverse events
   - Schedule next visit (4 weeks post-op)
3. **Week 4 Visit:**
   - Wound assessment
   - Document signs/symptoms of infection
   - Record adverse events

